## 7. Antibiotic exposures to subclinical pathogens overall

$$\left( \frac{N \text{ times any bacterial pathogen exposed to antibiotic} * \frac{\text{total number of diarrhea associated courses}}{\text{Total number of linked diarrhea associated courses}}}{\text{Total number of linked courses}} \right) * \left( \frac{\text{Total number of courses}}{\text{Total child years of follow up}} \right) * 100$$

To estimate the expected reductions in #1-7 listed above, we will compare the relative and absolute differences between the vaccine and no vaccine simulations.

Relative difference, is expressed as a ratio of the metric between the vaccine simulations and the no vaccine simulation, which will be calculated as:

$$\frac{\text{vaccine simulation}}{\text{no vaccine simulation}}$$

Or the percent change as:

$$\frac{\text{vaccine simulation} - \text{no vaccine simulation}}{\text{no vaccine simulation}}$$

Absolute difference, which captures the true distance between two values, will be calculated as:

$$| \text{vaccine simulation} - \text{no vaccine simulation} |$$

As a secondary outcome, we will estimate the average age of *Shigella* diarrhea under the vaccine and no vaccine scenarios to determine whether the vaccine would be expected to increase the average age of disease.

Future directions:

Once we have the *Shigella* vaccine simulation running, we will compare the impact of a *Shigella* vaccine to that for other enteric vaccines, most importantly rotavirus. We may also include a comparison to a broad stewardship intervention that is not targeted to a specific pathogen.

Added Sept 12, 2022:

We will estimate the expected reductions in diarrheal episodes caused by *Shigella* and any etiology (regardless of whether the episode was treated):

1. Severe *Shigella* diarrhea episodes

$$\left( \frac{N_{\text{severe diarrhea episodes attributed to Shigella}} * \frac{\text{total number of diarrhea episodes}}{\text{Total number of diarrhea episodes validly tested by TAC}}}{\text{total child years of follow up}} \right) * 100$$

2. *Shigella* diarrhea episodes

$$\left( \frac{N_{\text{diarrhea episodes attributed to Shigella}} * \frac{\text{total number of diarrhea episodes}}{\text{Total number of diarrhea episodes validly tested by TAC}}}{\text{total child years of follow up}} \right) * 100$$

3. Severe diarrhea episodes of any etiology

$$\left( \frac{N_{\text{reported severe diarrhea episodes}} * \frac{\text{total number of diarrhea episodes}}{\text{Total number of diarrhea episodes validly tested by TAC}}}{\text{total child years of follow up}} \right) * 100$$

4. Diarrhea episodes of any etiology

$$\left( \frac{N_{\text{reported diarrhea episodes}} * \frac{\text{total number of diarrhea episodes}}{\text{Total number of diarrhea episodes validly tested by TAC}}}{\text{total child years of follow up}} \right) * 100$$

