### Analyses:

#### Probabilistically sample observed episodes as “prevented” by vaccine and re-calculate incidence

We will start with a vaccine for *Shigella* with dosing at 6 and 9 months of age. We will assume 60% efficacy 14-days after administration of the second dose. For simplicity, we will assume 0% efficacy prior to this time point. The Monte Carlo simulation will then be performed over the dataset with 50,000 samples under two scenarios: vaccine and no vaccine. For the vaccine scenario, we will probabilistically assign whether diarrheal episodes attributable to *Shigella* (defined by AFe > 0.5) would have been prevented assuming 60% efficacy. It is important to note that *Shigella* infections increase with age therefore, 60% efficacy will not directly translate to a 60% reduction in diarrheal illnesses. Additionally, there is low natural immunity (~20%) against subsequent *Shigella* diarrhea when considering all serotypes and species, so prior infection will not be factored in (Rogawski McQuade 2020 J Infect Dis),

at least initially. In a later iteration of the analyses, we may incorporate potential clustering of prevented episodes within children (i.e. all episodes among 60% of children are prevented, rather than 60% of episodes prevented overall, regardless of the child). We may also incorporate the potential for herd immunity among children too young to be vaccinated, partial efficacy after a single vaccine dose, different vaccine schedules (6&9, 9&12, 12&15 months), effects on severity in addition to or instead of incidence, and varying levels of vaccine efficacy. For the no vaccine scenario, no *Shigella*-attributable episodes would be prevented. We will conduct a sensitivity analysis where we define shigella diarrhea by any detection of shigella rather than AFe > 0.5.

We will estimate the expected reductions due to a *Shigella* vaccine in the following metrics:

1. Antibiotic treated severe *Shigella* diarrhea episodes

$$\left( \frac{N_{\text{antibiotic treated severe diarrhea episodes attributed to Shigella}} * \frac{\text{total number of diarrhea associated courses}}{\text{Total number of linked diarrhea associated courses}}}{\text{total child years of follow up}} \right) * 100$$

2. Antibiotic treated *Shigella* diarrhea episodes

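### In the initial scenario the simulated mean age of Shigella diarrhea can only fall or stay unchanged, so the secondary outcome cannot show whether vaccination raises it

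*Protocol*

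**What the plan says.** The subsection of Analyses on sampling episodes as prevented sets out the starting model:

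- Schedule: "We will start with a vaccine for *Shigella* with dosing at 6 and 9 months of age".
- Protection: "We will assume 60% efficacy 14-days after administration of the second dose", with no waning stated. Before that point: "For simplicity, we will assume 0% efficacy prior to this time point".
- Mechanism: each observed Shigella-attributable episode is randomly classed as prevented or not. No step delays, re-times or adds an episode.
- Comparator: "For the no vaccine scenario, no *Shigella*-attributable episodes would be prevented".
- Natural immunity: taken as low (about 20%), "so prior infection will not be factored in". The sentence then limits this exclusion to the first stage of the work.
- Age pattern: "It is important to note that *Shigella* infections increase with age". No age distribution or age range is given.

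The same subsection lists things that may be added later: clustering within children, herd immunity in children too young for vaccine, partial one-dose efficacy, other schedules, severity effects and other efficacy levels. The Summary words several of these more firmly, as scenarios to be estimated.

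After metric 7, the secondary outcome compares the average age of Shigella diarrhea under the two scenarios "to determine whether the vaccine would be expected to increase the average age of disease".

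**The concern.** The stated question is whether the mean age rises. In the starting model, protection acts only at older ages and acts only by removal. Vaccination raises age at disease through postponed infection, lost natural immunity or waning, and none of these is in the initial model. The direction of the result is therefore known before any data are read.

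The risk lies in interpretation. A lower mean age, estimated from a large simulation with a narrow bootstrap interval, could be read as evidence that a Shigella vaccine would not move disease to older ages. It would in fact restate the assumed start of protection.

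**Working it through.** The protocol states no mean age or expected shift, so there is no figure of its own to reproduce.

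**Inputs from the protocol.** Efficacy VE = 0.60 from 14 days after a dose at 9 months, so the cut-off is c = 9 + 14/30.4375 = 9.46 months. Efficacy is 0 before c. The comparator removes nothing.

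**Assumed inputs.** Episodes span 0–24 months, with a flat, linearly rising or quadratically rising age density.

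**Sign.** Let f be the share of Shigella episodes before c, and let m_young and m_old be the mean ages before and after c. After thinning, the weight on young episodes rises from f to f / [f + (1 − VE)(1 − f)]. Hence

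change in mean age = −[f(1 − f)VE / (1 − (1 − f)VE)] × (m_old − m_young).

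Every episode after c is older than every episode before it, so m_old > m_young. The change is negative for any 0 < f < 1 and VE > 0, and zero only if f = 0 or f = 1. No age density enters this argument.

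**Size, 6 and 9 month schedule, VE 60%.**

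| Density | f | New weight on young | m_young | m_old | Mean without vaccine | Mean with vaccine | Change |
|---|---|---|---|---|---|---|---|
| Flat | 0.394 | 0.619 | 4.73 | 16.73 | 12.0 | 9.3 | −2.7 |
| Linear | 0.155 | 0.315 | 6.31 | 17.78 | 16.0 | 14.2 | −1.8 |
| Quadratic | 0.061 | 0.140 | 7.09 | 18.71 | 18.0 | 17.1 | −0.9 |

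For the linear case: 0.155 × 0.845 × 0.6 / (1 − 0.845 × 0.6) = 0.16, and 0.16 × (17.78 − 6.31) = 1.8.

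**Other schedules and efficacies.** With a declining density added, three schedules, four densities and VE of 20, 40, 60 and 80% give 48 combinations. The change is negative in all 48.

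**Sampling noise.** In 1,000 runs of 50,000 rows, with an assumed Shigella share of 5, 10 or 20% and the three densities tabulated above, the standard deviation of the difference was about 0.05–0.12 months for paired samples and 0.10–0.22 for independent ones. An increase occurred in 0 of 1,000 runs in every setting.

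**Listed extensions** (6 and 9 month schedule; flat / linear / quadratic, months):

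| Extension | Change |
|---|---|
| Partial efficacy after dose 1, assumed 30% | −2.6 / −1.5 / −0.7 |
| 30% indirect protection in the too-young only, VE 60% | −1.7 / −1.0 / −0.5 |
| Indirect protection equal at all ages, VE 60% | −2.7 / −1.8 / −0.9 |
| Clustering by child (linear only) | −1.8 |
| Effect on severity only | 0, as no episode is removed |
| 70% indirect in the too-young, VE 60% | +0.8 / +0.4 / +0.2 |
| 30% indirect in the too-young, VE 20% | +0.4 / +0.2 / +0.1 |

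With indirect protection confined to too-young children, the sign turns positive only when the reduction assigned to them exceeds the reduction at vaccinated ages. That is an input.

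**Would adding natural immunity help?** Losing 20% protection multiplies later risk by at most 1/0.8 = 1.25, so the residual after c is at most 0.4 × 1.25 = 0.5, against 1.0 before c. With 0.5 throughout, the change is −2.1 / −1.3 / −0.6. With the residual rising from 0.4 at c to 0.5 at 24 months, it is −2.3 / −1.3 / −0.5. The mean still falls.

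**Would waning help?** If efficacy is assumed to end abruptly at 15 months, the change is about 0 / +0.6 / +0.7. An increase becomes possible, but it depends on the assumed duration.

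**The case against.** The strongest reply is that the plan is staged. The exclusion of prior infection applies only at first, clustering by child is foreseen, and the Summary names indirect protection, severity-only effects and a range of efficacies. A reader might infer that nothing in this plan could raise the mean age. The protocol does not support that: a severity-only vaccine leaves the mean unchanged, and 30% indirect protection with 20% efficacy raises it. The claim must therefore be confined to the initial scenario. What survives is that in the extensions examined, one at a time, the sign is again set by what the analyst enters.

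A reader might also infer that the data contribute nothing. That goes too far. The observed age distribution determines how large the shift is, and the age profile of residual disease is a legitimate descriptive result.

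A third inference would be that the authors intend to report the absence of an upward shift as a finding. The protocol does not commit to that. The risk comes from the stated purpose of the outcome.

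Finally, this is one sentence about a secondary outcome in a simulation of a hypothetical vaccine. That limits the weight of the point but does not make the outcome able to answer its question.

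**Conclusion.** The point holds for the initial scenario. With no efficacy before about 9.5 months, 60% after, random deletion and no infection history, the expected mean age of residual Shigella diarrhea can fall or stay unchanged but cannot rise. The stated purpose of the secondary outcome cannot be met there. In the listed extensions taken singly, the direction follows from the inputs and the data inform the magnitude.

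The sign rests only on the protocol's own model. The falls of 0.9 to 2.7 months rest on assumed age patterns over an assumed 0–24 months and should not be read as expected effects. Metrics 1–7 and the diarrhea incidence metrics added in September 2022 are unaffected.

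**What to change.** Reword the secondary outcome as descriptive: report the age distribution and mean age of prevented and of residual Shigella episodes in each scenario. Add a sentence saying that the direction of any shift in mean age follows from the assumed onset of protection (and, where used, the assumed indirect protection), and is not evidence for or against an upward shift in age at disease.

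Drop the aim of assessing an increase unless a later iteration includes a mechanism able to produce one, such as waning efficacy or delayed infection. Report any such result as conditional on that assumption, over a range of values. Adding only the loss of the roughly 20% natural protection would not be enough under the age patterns examined.

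The cost is one or two sentences of text and a tabulation from output the simulation already produces. The optional waning or delay model is modest extra coding.
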